#### Recruitment of participants

Potential participants will be recruited from walk-in customers who present at participating pharmacies seeking advice or products for an ear complaint. Pharmacists will invite these patients to participate in the study, provide an information sheet (with verbal explanation), ensure patient meets eligibility criteria and completes an informed consent form. Informed consent obtained from study participants is in written form.

### Participant eligibility criteria

To be eligible for participation in the study, patients must:
Be aged 13 years or older (to be able to independently provide informed consent, those between 13-16 years can consent for self or parent/guardian may provide consent).Be able to understand the English language at a level appropriate to provide informed consent (pharmacists will use professional judgement to determine if participants are able to provide informed consent).Attend a participating pharmacy as a ‘walk-in’ customer seeking help for an ear complaint.

Patient will be excluded from the study if they:
Are < 13 years oldHave inadequate health literacy or English language skills to provide informed consentHave obvious major trauma to the earAre a high COVID-19 risk patient (e.g. travelled in a COVID-19 hotspot within 14 days)Have not consented

### Intervention participants

Participants' temperature will be measured in the waiting area, if > 37.5 Celsius COVID-19 precautions will be implemented and additional personal protection equipment (PPE) applied, including face mask, gloves and face shield. Pharmacists will conduct the consultation with eligible consenting participants in a private consultation space. Pharmacists will then document a brief history of the ear complaint including symptoms, duration and treatments tried by the patient on a template service summary document (Appendix 1) provided to them. Pharmacists will then examine the ears using otoscopy and tympanometry. If the complaint is hearing related, pharmacists will perform a hearing screening test using the *Sound Scouts* application [17]. *Sound Scouts* is an application based hearing check that can be used in persons over the age of 4 years to detect conductive hearing loss, sensorineural hearing loss and difficulties listening in noise [17].

### Equipment

The otoscope used in this study is the MedRx video otoscope. The tympanometer is the Amplivox Otowave 102. Hearing screening will be conducted using the *Sound Scouts* application with Senheiser HD 300 headphones.

### Patient data collection

Patient data collected includes full name, postcode, age, gender, allergies, medicines, medical conditions, pregnancy/breastfeeding status, temperature, brief history of the ear complaint including symptoms, duration and treatments tried by the patient, otoscopy, tympanometry and hearing screening findings/results. This information will be documented on the service summary record. This record will contain all the information collected by the pharmacists from the patient consultation. It was developed in consultation with an advisory group (consisting of stakeholder representatives from various organisations in the health sector), is formatted in Microsoft Office and is stored on a password protected hard drive.

### Protocol

Pharmacists will follow a protocol to determine the pathway (Fig. 1) for the patient. If otoscopy and tympanometry assessments are normal and hearing is not affected, the pharmacist may recommend no treatment and advise patient to monitor and seek medical advice if condition does not improve or worsens. If otoscopy indicates excessive wax only or moisture retention from water activity only and no other symptoms are present, the pharmacist may recommend pharmacy products including ear drops containing drying agents or wax dissolvents. All other patients will be referred to a GP with an appointment made by the pharmacist before they leave the pharmacy. Pharmacists will be able to book appointments with the GPs via a public online booking platform or via telephoning the GP practice. If the pharmacist is unable to make a timely appointment with a GP, the patient will be recommended to attend the local emergency department. Participants will be asked to complete a patient satisfaction survey and consent to a follow-up phone call in 7 days.

**Fig. 1 Fig1:**
[figure not shown]
LISTEN UP study protocol pathway

#### GP referral

The GP to which the patient has been referred will be emailed a password encrypted file with all of the patient data including temperature, brief history of the ear complaint including symptoms, duration and treatments tried by the patient, otoscopy, tympanometry and hearing screening findings/results.

#### Pharmacist recommendations

Pharmacists will be asked to record their actual recommendations and recommendations they would have made if they had an expanded scope including if they would have recommended a prescription medicine or referral to other service providers including audiometrists, speech pathologists, or ear, nose and throat specialists. This information will be collected for research purposes only as current practice does not allow Australian pharmacists to recommend prescription medicines or refer patients to specialty services.

### Follow-up

A member of the research team will phone all patient participants 7 days after their pharmacy consultation to explore the patient outcomes from the intervention. Patients will be asked about the condition of their ear complaint (improvement/deterioration), their satisfaction with the pharmacy intervention (Likert scale), if they were referred to a GP, if they attended the GP appointment and what advice, prescription or referral they had received from the GP. If the patient indicates further deterioration of the condition, a lack of improvement or a concern about the complaint, the researcher will offer to refer the patient to the GP and/or advise the patient to seek further medical advice.

### Data saturation

Total population sampling will be conducted in this study. We will attempt to interview all GPs and pharmacists by inviting them to participate in an interview three times. In addition, all participants will receive a follow-up phone call four times, including at least one out of normal business hours, in an attempt to ensure as many as possible participants receive the follow-up phone call.

### Study measurements and outcomes

Data pertaining to patient, pharmacist and GP experiences of the ear health intervention will be collected via semi-structured interviews pre- and post- intervention with pharmacists and GPs, service summary documentation, patient satisfaction surveys and 7-day follow-up interviews with patients. These data collection tools were developed in house to suit this innovative model. Pharmacist and GP interviews will include questions pertaining to perceptions of expanded pharmacy services, current local landscape of ear health (incidence, access to services) and expected/actual outcomes of the LISTEN UP project including pharmacist capacity, patient receptiveness and GP/pharmacist/patient interaction. Usual care data will be recorded for 8 weeks prior to the intervention. The usual care data will include a non-identifiable record of ear complaints presenting to the pharmacy, the description of the complaint and the pharmacists recommendations (Table 1).

**Table 1 Tab1:** Data collection methods for pre-, during and post-intervention phases

	Patients	Pharmacists	General practitioners
Pre-intervention	Record of usual care in pharmacy for 8 weeks	Semi-structured interview	Semi-structured interview
During intervention	Patient satisfaction survey	Service summary document	
Post-intervention	Semi-structured interview (7-day follow-up)	Semi-structured interview	Semi-structured interview

Usual care data will record patient age groups, type of complaint (ear pain, ear wax, swimmers ear, ear itch, hearing loss or other), duration of the complaint, pharmacist recommendations (pharmacy products, verbal GP referral, verbal emergency department referral or other).

Initial study measurements are pharmacist and GP perspectives of ear health in the community, this described study protocol, expected outcomes, and anticipated enablers and barriers. This data will be collected prior to the study beginning via semi-structured interviews to explore the expected feasibility of the study. The interviews will be repeated post-study and the data collected from pre-intervention will be compared with data collected from these interviews to measure a change of opinion with pharmacists and GPs post-intervention.

Pharmacists will record the consultation data on a service summary document (Appendix 1). This document will also collect pharmacist recommendations for the patient, including they would have made if they had an expanded scope of practice such as prescription medicines and specialist referrals. This data will be compared with data provided by the patients at the 7-day follow-up phone call about the medicines they were prescribed and any referrals they may have received. In addition, qualitative data relating to the patient experience of the pharmacy service and patient perceived outcomes of the ear complaint will be collected during the patient interviews.

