## Methods and design

### Study design and setting

This is a longitudinal pre- and post-design study of a community-pharmacy-based intervention piloted in two rural community pharmacies in Queensland, Australia. Co-design has been applied to this study with stakeholder, health professional, pharmacist and consumer perspectives from previous research utilised in conjunction with community consultation to inform the design of this study [8–10]. Prior to the intervention, participating pharmacies will collect usual care data for 8 weeks beginning November 2020. The intervention will then be piloted for 6 weeks at each pharmacy and then refinement and improvements will be made before the longitudinal impact study is conducted for 12 months.

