##### Primary

To evaluate the feasibility, acceptability and potential effectiveness of a community pharmacy-based intervention for ear health by exploring:
Pharmacist views of:
i.Pharmacist capacity and competence to provide the intervention (motivation, confidence, competence, experience of training, capacity (workflow/workload))ii.Patient acceptanceiii.Pathway to GP service (timeliness of appointment, GP staff attitudes)Patient views of the service in terms of access, alternative health care options, satisfaction and willingness to pay (confidence/acceptance of pharmacist service, referral process, timeliness of pharmacists consult/GP consult).GP views on appropriateness of pharmacist referrals, collaborative care with pharmacists (use of telehealth).To evaluate the use of otoscopy and tympanometry by pharmacists to improve specificity of ear condition management in community pharmacy by comparing:
Usual care data with intervention data pertaining to pharmacist recommendations.Pharmacist recommendations on the patient service summary record compared to GP prescriptions and referrals described by patients at the 7-day follow-up phone call.Patient acceptance of pharmacists performing examinations with an otoscope and tympanometer.

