### Data analysis

Data collected via semi-structured interviews will be transcribed verbatim and thematically analysed both inductively and deductively, using the NVivo 12 software programme [18, 19]. Data collected from the patient surveys and patient service summary record will be analysed using descriptive statistics and frequencies using IBM SPSS Statistics 25 for Windows.

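### The usual-care versus intervention comparison of pharmacist recommendations, a primary outcome, sets different populations and calendar periods side by side with no common analysis set

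*Protocol article*

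**What the plan says.** The second primary outcome in the protocol article (Study outcomes, Primary) evaluates pharmacists' use of otoscopy and tympanometry. Its first comparison, called 2a here, is "Usual care data with intervention data pertaining to pharmacist recommendations".

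**Usual-care side.** Study design and setting says that "participating pharmacies will collect usual care data for 8 weeks beginning November 2020". Study measurements and outcomes describes the material as "a non-identifiable record of ear complaints presenting to the pharmacy". On content it says "Usual care data will record patient age groups, type of complaint", then lists six complaint categories (pain, wax, swimmer's ear, itch, hearing loss, other), duration and recommendation. The age cut-points are not given. No age limit, exclusion or consent step is stated for this record.

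**Intervention side.** After a 6-week pilot, "refinement and improvements will be made before the longitudinal impact study is conducted for 12 months". Patients must "Be aged 13 years or older". They are excluded for obvious major ear trauma, high COVID-19 risk, or English or health literacy too limited for consent. Recruitment of participants adds: "Informed consent obtained from study participants is in written form".

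**Analysis.** Under Data analysis, the survey and service-summary data "will be analysed using descriptive statistics and frequencies". That section does not name the usual-care record, and no restriction, matching or stratification is stated for 2a. The limitations section discloses that there is no control group. It does not mention that the two sides differ in age, season or consent.

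**The concern.** The abstract calls this a single-cohort pre- and post-test study, but for 2a the two sides are different sets of patients, gathered under different rules at different times. A before-after contrast of that kind is open to case mix.

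The article itself gives reasons to expect case mix to matter:

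- **Complaint type drives the recommendation.** Under the heading Protocol, wax alone, or water-related moisture alone, may be managed with pharmacy products. Abnormal findings outside those groups go to a GP. The balance of complaints therefore feeds straight into the split between product and referral, at least on the intervention side. Swimmer's ear is one of the usual-care categories and plausibly varies with season.
- **Children may be present on one side.** Background reports middle-ear disease in up to 50% of rural and remote children under 3. That is a community prevalence, not a share of pharmacy presentations. Still, nothing stated keeps under-13s out of the usual-care record, and they cannot enter the intervention.

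At stake is the reading of a primary outcome. A change in referral or product share could be credited to the examinations when it came from who was counted and when.

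**Working it through.** **1. The plan's own figure.** The only sample-size calculation is for one proportion: n = Z²P(1−P)/d² = 1.96² × 0.14 × 0.86 / 0.05² = 185. Adding 10% gives 185 × 1.10 = 203.5, stated as 203. It reproduces, but it rests on the prevalence of hearing loss and does not size 2a.

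**2. Calendar overlap.** Eight weeks is 8/52 = 15% of a year. The start day in November is not stated.

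| Start (2020) | Last of 56 days | Days from 1 December on |
|---|---|---|
| 1 November | 26 December | 26/56 = 46% |
| 15 November | 9 January | 40/56 = 71% |
| 30 November | 24 January | 55/56 = 98% |

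The window is late spring to summer, in a proportion that depends on the start day. A full 12-month impact study would include the same weeks once.

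**3. Size of a false difference when the intervention does nothing.** The article gives no referral rates, no share under 13 and no complaint mix, so every input here is assumed. Differences are usual care minus intervention, in the share referred.

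- *Complaint mix:* difference = shift in mix × gap in referral rate between complaint types. A shift of 10 to 30 points with a gap of 20 to 60 points gives 0.10 × 0.20 = 2 points up to 0.30 × 0.60 = 18 points.
- *Age:* difference = share under 13 × gap in referral rate between ages. A share of 10% to 40% with a gap of 20 to 40 points gives 0.10 × 0.20 = 2 points up to 0.40 × 0.40 = 16 points.

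**4. Direction.** One set of specific assumptions:

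- Under-13s referred at 60% and older patients at 30%, with 10% to 40% of records under 13: 0.10 × 0.30 = +3 to 0.40 × 0.30 = +12 points. With 50% and 40% instead: +1 to +4.
- Swimmer's ear at 30% to 50% of usual-care complaints against 20% over the year, referred at 20% against 50% for other complaints: 0.10 × (−0.30) = −3 to 0.30 × (−0.30) = −9 points.

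If the two simply added, the net would lie between 3 − 9 = −6 and 12 − 3 = +9 points. Even the sign is undetermined.

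**5. What the listed fields allow.**

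| Source of difference | Can it be handled? |
|---|---|
| Age | Yes, if the usual-care bands break at 13 (not stated) |
| Complaint type | Yes, if intervention complaints are coded to the same six categories. The service summary is described as a history of the complaint, without those categories |
| Season | Partly, by comparing the same calendar weeks |
| Trauma, COVID-19 risk, language, willingness to consent | No. None is a listed usual-care field |

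**The case against.** **Silence is not content.** A reader might infer that usual care is a record of all comers and that children will certainly appear only there. The article does not say so. It states no restriction, but the form is not shown and the age groups could already break at 13. What stands is that the described populations are not the same and no common set is defined.

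**The season is easily overstated.** A reader might infer a wholly summer baseline. The text says only that collection begins in November, and with a 1 November start more than half the days fall in spring.

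**Analysis detail can sit in a statistical analysis plan.** That is fair for the method of stratification. It does not cover the data: if the age break and common complaint coding are not collected, no later plan can supply them.

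**The limitation is disclosed and the study is a pilot.** The article admits the lack of a control group, calls for a larger controlled study, and speaks of potential effectiveness. 2a is one item among several, most of which concern views and acceptability. This lowers the weight considerably. It does not remove the point, because the differences in age and coding are avoidable without a control group.

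**The record may already be complete.** Collection was due from November 2020 and the article's identifier carries 2021, so changing the form may no longer be possible. This affects which remedy is available, not whether the comparison is sound.

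**Conclusion.** The point holds in a limited form. As described, 2a compares groups that differ in calendar period, in consent and eligibility and, unless the form already prevents it, in age. Nothing in the article brings them onto a common footing, so a crude difference in recommendations cannot be attributed to otoscopy and tympanometry.

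The size is unknown. The 2 to 18 and 2 to 16 point ranges show what is possible under assumed inputs, and the components may partly cancel. A reader might infer that the result will be biased by a particular amount or in a particular direction, or that a shift will certainly be reported as an effect. The documents support neither: they give no rates, and the stated analysis is descriptive with no hypothesis test for 2a.

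For an uncontrolled descriptive pilot this should be fixed, but it is not a reason to stop. It rests on reading the absence of a stated restriction on the usual-care record as meaning that none was applied.

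**What to change.** 1. **Common age range.** Define the 2a analysis set as age 13 or over in both periods, with a break at 13 in the usual-care age groups. If the record is already closed with a band that straddles 13, report 2a with and without that band.
2. **Common coding and stratified reporting.** Code each intervention complaint to the six usual-care categories, using the complaint as presented before examination so that otoscopy does not alter the category. Keep the pharmacy identity on every record. Report 2a stratified by, or directly standardised to, complaint type, and by pharmacy.
3. **Season.** Add a sensitivity comparison limited to impact-study patients seen in the same calendar weeks as usual care. This needs recruitment to run the full year, whereas the sample-size section speaks of up to 12 months.
4. **Interpretation.** State that consent selection and the other exclusions cannot be adjusted for from the recorded fields, add the age, season and consent differences to the limitations, and present 2a as descriptive.

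**Cost.** Items 1, 2 and 4 need a form line, a coding rule and wording. Estimates become less precise: six categories by two pharmacies is 12 cells, or about 200/12 = 17 intervention patients each, so sparse cells will need merging. The same-weeks subset is small. With even recruitment, 200 × 8/52 is about 31 patients. At an assumed proportion of 50%, the 95% half-width is 1.96 × √(0.25/31), about 18 points, against 1.96 × √(0.25/200), about 7 points, for all 200. It can therefore show only a gross seasonal discrepancy.

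**Optional.** Continuing the anonymous record for all presenters through the impact study would put like against like and show the share enrolled. It lasts 52/8 = 6.5 times as long as the planned log, adds to pharmacists' work and may need an ethics amendment.

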#### Study measurements

The study measurements collected in the intervention include pharmacist views, pharmacist recommendations, GP views and patient views. There measurements are aligned to the primary and secondary outcomes of the study (Table 2).

**Table 2 Tab2:** Summary of study measurements aligned to study outcomes

Measurement	Instruments	Pre-study	During study	Post-study	Primary outcome	Secondary outcome
Pharmacist views	Semi-structured interview	X		X	1a	1, 2
Pharmacist recommendations	Service summary document		X			1, 2, 3
GP views	Semi-structured interview	X		X	1c	1, 2
Patient views	Satisfaction Survey			X	1b	1, 2
Patient views	Semi-structured interview			X	1b	1, 2, 3

#### Study outcomes

The outcomes of this study will be assessed against the objective of implementing a rural community pharmacy-based ‘model of care’ to improve the management of ear complaints in the community.

##### Primary

To evaluate the feasibility, acceptability and potential effectiveness of a community pharmacy-based intervention for ear health by exploring:
Pharmacist views of:
i.Pharmacist capacity and competence to provide the intervention (motivation, confidence, competence, experience of training, capacity (workflow/workload))ii.Patient acceptanceiii.Pathway to GP service (timeliness of appointment, GP staff attitudes)Patient views of the service in terms of access, alternative health care options, satisfaction and willingness to pay (confidence/acceptance of pharmacist service, referral process, timeliness of pharmacists consult/GP consult).GP views on appropriateness of pharmacist referrals, collaborative care with pharmacists (use of telehealth).To evaluate the use of otoscopy and tympanometry by pharmacists to improve specificity of ear condition management in community pharmacy by comparing:
Usual care data with intervention data pertaining to pharmacist recommendations.Pharmacist recommendations on the patient service summary record compared to GP prescriptions and referrals described by patients at the 7-day follow-up phone call.Patient acceptance of pharmacists performing examinations with an otoscope and tympanometer.

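### Outcome 2b compares pharmacists with GPs who were sent the pharmacists' own ear findings, and the listed 7-day call items do not show whether the GP checked the ear

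*Protocol article*

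**What the plan says.** The second primary outcome (Study outcomes, Primary) concerns what otoscopy and tympanometry by pharmacists add to ear management. Its second comparison, 2b, is: "Pharmacist recommendations on the patient service summary record compared to GP prescriptions and referrals described by patients at the 7-day follow-up phone call". Study measurements and outcomes repeats it for the service summary data, which include what the pharmacist would have recommended under an expanded scope: "This data will be compared with data provided by the patients at the 7-day follow-up phone call about the medicines they were prescribed".

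Four other places bear on how that comparison can be read.

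- **Route to the GP** (Protocol section): "All other patients will be referred to a GP with an appointment made by the pharmacist before they leave the pharmacy". The text does not say whether the appointment is in person or remote.
- **What the GP is sent** (GP referral): the GP "will be emailed a password encrypted file with all of the patient data including temperature", and the list ends with "treatments tried by the patient, otoscopy, tympanometry and hearing screening findings/results".
- **What the patient is asked about the GP** (Follow-up): whether they were referred, "if they attended the GP appointment and what advice, prescription or referral they had received from the GP".
- **All data sources** (Study measurements and outcomes): "semi-structured interviews pre- and post- intervention with pharmacists and GPs, service summary documentation, patient satisfaction surveys and 7-day follow-up interviews with patients".

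Telehealth appears once in the article, in primary outcome 1c, as a bracketed topic of GP views: "GP views on appropriateness of pharmacist referrals, collaborative care with pharmacists (use of telehealth".

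**The concern.** Of the three comparisons under the second primary outcome, only 2b sets the pharmacist's judgement against another clinician's decisions. The others compare recommendations with usual care and measure patient acceptance of the examination. A reader wanting to know whether pharmacists' ear examinations lead to sound management will therefore look to 2b.

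Agreement with a GP carries most weight when the GP has looked at the ear. If the GP acts on the emailed findings without examining, agreement shows that two clinicians drew the same conclusion from one set of findings. It does not show that the findings were right. A GP on the phone or on video cannot perform otoscopy or tympanometry, and an in-person GP may or may not repeat them. The listed data put all these cases in one figure.

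Table 2 also links pharmacist recommendations and the patient interview to the third secondary outcome, evidence on the scheduling of medicines. An over-read 2b figure could therefore carry into a policy argument.

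**Working it through.** **No figure in the plan bears on this.** The article gives no expected agreement for 2b, no threshold and no share of remote consultations. Its one sample-size calculation concerns a single proportion: 1.96² × 0.14 × 0.86 / 0.05² = 185.01, and 185 × 1.10 = 203.5, against the stated 185 and 203. It reproduces and is unaffected.

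**Step 1: is the comparator independent?** GP referral sends the GP the pharmacist's history and test findings. The GP's prescription or referral is the comparator in 2b, so it comes from a clinician holding the pharmacist's findings. This holds for in-person and remote consultations alike.

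**Step 2: can the data show who checked the ear?**

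| Listed source | Per-patient GP information | Mode of consultation or GP ear examination |
|---|---|---|
| Service summary | None; completed by the pharmacist | Not available |
| Satisfaction survey | About the pharmacy service | Not listed |
| 7-day call | Referral, attendance, advice, prescription or onward referral | Not listed |
| GP interviews, before and after | General views | Not per patient |

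No listed source holds the information, so if it is not asked at the call it cannot be recovered later.

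**Step 3: what would pooling do?** Let *t* be the share of GP consultations without an ear examination, *a* the agreement when the GP examines and *b* the agreement when the GP does not.

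- Pooled agreement = (1 − t)·a + t·b
- Difference from the examined group = t·(b − a)

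All values below are assumptions, because the documents give none.

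| a | b | t | Pooled | Difference (points) |
|---|---|---|---|---|
| 0.60 | 0.95 | 0.10 | 0.635 | 3.5 |
| 0.60 | 0.95 | 0.30 | 0.705 | 10.5 |
| 0.60 | 0.95 | 0.50 | 0.775 | 17.5 |
| 0.50 | 1.00 | 0.25 | 0.625 | 12.5 |
| 0.60 | 1.00 | 0.25 | 0.700 | 10.0 |
| 0.70 | 1.00 | 0.25 | 0.775 | 7.5 |

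If b = a the difference is zero whatever t is. The table shows only that the effect depends on two quantities, t and b − a, that the listed data cannot supply. Nor is *a* itself free of dependence, since the examining GP has also been sent the findings.

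**The case against.** The strongest objection is that telehealth carries too much weight. It is mentioned once, as an interview topic. The described pathway leans towards local visits: practices within 25 km are invited, appointments are to be available within 48 h, the listed GP equipment includes nothing specific to telehealth, and the call asks about attendance. This stands. A reader might infer from 1c that remote GP consultations are planned or common, but the article supports neither. It only leaves them possible. Nor does 1c need a telehealth count beside it, because it is measured by GP interviews and analysed thematically.

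A second objection is that the 7-day contact is a semi-structured interview whose guide is not shown, so the questions may already be there. This stands as a limit on the claim, which concerns only the items the article lists.

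Third, a reader might infer that agreement is almost assured when the GP does not examine. The documents do not support that. The GP referral list names findings and not the pharmacist's recommendation, and a GP holding the same findings still decides whether to prescribe, what to prescribe and whether to refer. The dependence runs through shared findings. Agreement on management given those findings is also of some interest in its own right.

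Fourth, confining 2b to examined patients would not cure the problem. Those GPs were also sent the findings, and whether to examine is a decision made after referral. If GPs examine mainly when in doubt, that subset is selected. This stands and shapes the remedy.

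Finally, the study is a descriptive pilot without a control group and says so. That lowers the stakes but does not change what 2b can show.

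**Conclusion.** The point holds in a limited form, as an inexpensive improvement. The comparator in 2b is a GP who was sent the pharmacist's findings, and the listed data cannot separate decisions made after the GP checked the ear from decisions resting on those findings. Agreement may be partly inflated for this reason. By how much is unknown: the illustrative differences of 3.5 to 17.5 points rest wholly on assumed values and vanish if agreement is the same with and without examination.

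The conclusion assumes that the article's call items are the ones asked. If the unseen guide already covers mode and examination, only the reporting and wording changes below remain. The non-independence itself does not depend on telehealth and would be present if every GP visit were in person.

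**What to change.** 1. Add two items to the 7-day call described under Follow-up: *Was the GP consultation in person, by phone or by video?* and *Did the GP look in your ear?*
2. Report 2b for all referred patients who saw a GP, and split it by whether the GP examined the ear. Do not make the examined subset the sole main result.
3. Describe 2b as concordance with a GP who had the pharmacist's findings, not as independent validation of pharmacist otoscopy and tympanometry.

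The cost is two short questions on a call already planned and one extra split in a table. The answers rely on patient recall, and the subgroups will be small and possibly selected, with wider intervals. No sample-size figure changes.
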